### Process and implementation evaluation

The process and implementation evaluation will aim to understand variations in the impact of the intervention on outcomes of interest and to contextualise findings. Activity data will be integrated with planned process evaluations using both quantitative and qualitative methods. We will interview 30 women in both intervention and control groups to assess acceptability and explore experience. Sampling for interviews will be based on maximum diversity in relation to age, socio-demographic characteristics, parity and obstetric history. Trial recruitment and retention will be assessed by examining eligibility, participation and attrition rates. Fidelity will be assessed through routine monthly audits and include access to care, completeness of antenatal care, content of the intervention, continuity of care (number of midwives seen), referrals. Up to 20 key stakeholders including midwives, clinicians, managers and commissioners will be interviewed regarding acceptability of working in a new model of care and the impact on the wider organisation.

### Data analysis

#### Sample size calculation

There is no pre-existing precise data for the composite outcome that we plan to use. However, we consider that a 15% increase in the rate of appropriate interventions is both feasible and clinically useful. With six WTE midwives in the POPPIE team, we can randomise 175–210 women to the active intervention (35 bookings per year per midwife) during a 12-month period. The standard care arm is limited by the total number of women available, which is likely to be less than 400 per year. With 175 women in each arm (350 in total), we would have 80% power to detect a 15% increase in the rate of appropriate interventions (from 40 to 55%) (calculated using the Stata version 14.2 (StataCorp, College Station, TX, USA)).

#### Proposed statistical analysis

The analysis will be ‘intention to treat’, including withdrawals and losses to follow-up. Randomisation should ensure that the groups are similar or equivalent in their baseline characteristics; additional multivariate analysis will be used if baseline differences are noted between the two groups.

The relative risks (with 95% confidence intervals) of the component primary outcomes will be calculated. Secondary outcome measures of categorical data will be analysed with *χ*^2^ tests and continuous data will be analysed with *t* tests (for normally distributed data). Ranked or Likert-scale data will be analysed using cumulative odds ratios. Logistic regression and multiple linear regressions will be used if necessary to adjust for any other confounding variables. Outcome assessments and analysis will be blinded.

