### Identification, screening, recruitment and randomisation

Trial information will be available in all relevant clinical areas including maternity services, general practice surgeries and health centres. Community midwives and other maternity care clinicians will refer women who express an interest in the study to the midwifery team leader to discuss trial participation. At early nuchal and/or anomaly ultrasound scan appointments, women who meet inclusion criteria will be offered verbal and written information about the study. Potentially eligible women will also be identified by review of medical records and appointment lists by clinical staff. In these cases, women will be contacted by a member of the direct clinical team to discuss their eligibility and study participation and sent a leaflet by post/email to read (if interested) before their appointment attendance. Adequate time will be given to interested women to explain the study, for considering participation, and asking any questions with members of the clinical team. All participants will provide written informed consent prior to participation.

Baseline data will be collected, and participants randomised in a 1:1 ratio to receive either POPPIE care or routine standard care. Randomisation will be managed via a secure web-based randomisation system (MedSciNet™), which is part of a password-protected Internet-based study specific data management system. A minimisation algorithm will be used to ensure balance between the groups with respect to smoking at booking and previous PTB (< 37 weeks). The nature of the intervention is such that blinding of participants and care providers cannot be achieved. However, risk of bias will be reduced since data will be processed by researchers blinded to the model of care that the women is allocated to. The flow diagram of participants though the study is shown in Fig. 3.

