### Outcomes and measures

#### Primary outcomes

The composite primary outcome is the initiation of any of the following interventions appropriately provided for the prevention and/or management of preterm labour and birth (antibiotics for urinary tract infections, smoking cessation and domestic violence advocacy referrals, transvaginal scan assessments of the cervix, fetal fibronectin assessments, cerclage insertion, progesterone administration, corticosteroid administration, magnesium sulphate administration, admission for observation and in utero transfer). A composite outcome is chosen, as the primary outcome as powering a pilot trial for PTB alone would require too large a sample size, and helps the investigators to avoid an arbitrary choice between several important outcomes that refer to the same disease process [25]. We will report the effect of the continuity of care model on both the composite and its components for all woman in the study, specifying if (1) an intervention was required and (2) the intervention was provided. Women who experience any one of the intervention components will be considered to have experienced the composite outcome.

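### Adjustment depends on observed baseline differences, so the two minimisation factors will rarely enter the analysis; if they predict the composite, the unadjusted result is conservative and some power is forgone

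*Protocol article*

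**What the plan says.** Under Identification, screening, recruitment and randomisation, the protocol article states: "A minimisation algorithm will be used to ensure balance between the groups with respect to smoking at booking and previous PTB" (defined as birth before 37 weeks). Allocation is 1:1.

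Under Proposed statistical analysis, it plans the following: "The relative risks (with 95% confidence intervals) of the component primary outcomes will be calculated". Secondary outcomes get chi-squared tests, t tests or cumulative odds ratios. Two sentences deal with adjustment. The first is conditional on what is seen at baseline: "additional multivariate analysis will be used if baseline differences are noted between the two groups". The second is open-ended: "Logistic regression and multiple linear regressions will be used if necessary to adjust for any other confounding variables". The section does not name the minimisation factors, and it gives no criterion for what counts as a difference or as necessary.

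Under Primary outcomes, a woman meets the composite through any one component. The components include "smoking cessation and domestic violence advocacy referrals, transvaginal scan assessments of the cervix", and also progesterone and cerclage.

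**The concern.** The trigger works against the design. Factors used in minimisation are the ones least likely to look different between arms, so a rule that waits for a visible difference will almost always leave them out. Yet balance is no reason to omit them. When allocation is forced to balance on a factor that predicts outcome, the treatment estimate varies less from trial to trial than the unadjusted standard error assumes. Intervals are then wider than they need be and the test rejects too seldom under the null.

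Both factors are plausibly prognostic here. Smokers can meet the composite by a smoking-cessation referral. Previous PTB bears on cervical surveillance and on the interventions that follow from it: the Obstetric care pathway section says that women with specific risk factors go to the cervical scan clinic and that further tests and treatments depend on risk factors.

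A second fault does not depend on prognostic strength. Under the stated rule, the covariates of any adjusted analysis are chosen after looking at the baseline table, so chance imbalance determines which they are.

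**Working it through.** **1. The plan's own figure.** The Sample size calculation section gives "With 175 women in each arm (350 in total") and says "we would have 80% power to detect a 15% increase in the rate of appropriate interventions", from 40% to 55%. Alpha is not stated there; two-sided 5% is assumed, in line with the 95% intervals.

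- Pooled rate: (0.40 + 0.55)/2 = 0.475.
- Null SE: √(2 × 0.475 × 0.525/175) = 0.0534.
- Alternative SE: √((0.24 + 0.2475)/175) = 0.0528.
- Power: Φ((0.15 − 1.96 × 0.0534)/0.0528) = Φ(0.86) = 80.5%.

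The stated 80% reproduces. This is the power of an unadjusted comparison of two proportions.

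**2. Simulation of the design.** 350 women were minimised on two binary factors, with 4,000 trials per scenario. Marginal rates were 40% in both arms (null) or 40% and 55% (alternative). The unadjusted two-proportion test was compared with logistic regression that included both factors. Assumptions not in the documents: 30% smokers, 40% with previous PTB, independent factors with the same odds ratio for each, probability 0.8 of allocation to the favoured arm, no dropout. The last column is the mean model SE of the unadjusted log relative risk divided by its actual standard deviation, under the alternative.

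| Odds ratio per factor | Type I error, unadjusted / adjusted | Power, unadjusted / adjusted | SE ratio |
|---|---|---|---|
| 1 | 5.1% / 5.1% | 80.4% / 80.5% | 1.00 |
| 1.5 | 4.7% / 4.9% | 80.4% / 81.3% | 1.01 |
| 2 | 4.2% / 4.9% | 81.3% / 83.0% | 1.02 |
| 3 | 3.6% / 5.0% | 80.3% / 83.9% | 1.04 |
| 5 | 3.1% / 4.9% | 82.3% / 88.5% | 1.11 |

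Monte Carlo error is about 0.3 to 0.4 points for type I error and 0.6 points for power.

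**3. Hand check of the last row.** With those prevalences, 0.7 × 0.6 = 42% of women have neither factor, 0.3 × 0.6 + 0.7 × 0.4 = 46% have one, and 0.3 × 0.4 = 12% have both. At an odds ratio of 5 per factor, rates of 1/6, 1/2 and 5/6 give the required margin: 0.42/6 + 0.46/2 + 0.12 × 5/6 = 0.07 + 0.23 + 0.10 = 0.40.

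- Variance used by the unadjusted test: 0.40 × 0.60 = 0.24.
- Variance left within strata: (0.42 + 0.12) × 5/36 + 0.46 × 1/4 = 0.075 + 0.115 = 0.19.
- SE ratio under exact balance: √(0.24/0.19) = 1.12.
- Effective critical value: 1.96 × 1.12 = 2.20, a type I error of about 2.8%.

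The simulated 1.11 and 3.1% are slightly milder, as expected, because minimisation with a random element does not balance every stratum exactly.

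**4. Sensitivity to the assumptions.** Other simulations gave the same direction. With only previous PTB prognostic, power was about 82% unadjusted and 86% adjusted. Entry needs only one risk criterion, so smoking and previous PTB may be negatively associated. An illustrative mix of 25% neither, 35% smoking only, 35% previous PTB only and 5% both gave 82% and 86%, with unadjusted type I error of 4.7%. The size of the effect therefore moves with the assumptions, and the gain in power was about 1 to 6 points in a further set of runs.

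**The case against.** The strongest reply is that nothing here invalidates a conclusion. The error is conservative, the unadjusted analysis keeps the power the trial was designed for, and this is a pilot meant to inform a larger trial. That stands, and it limits the severity.

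A second reply is that this is a condensed article and covariate lists usually sit in an analysis plan that is not shown. This is right about the list: silence on covariates alone would be no finding. It does not cover the trigger, which the article states as a rule.

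There are also stronger readings that a reader might infer and that the documents do not support:

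- **The trial is underpowered or its type I error is inflated.** Neither follows. Power is forgone relative to a better analysis, not relative to the design, and unadjusted type I error is at or below about 5%.
- **The loss is certain and large.** It is conditional on the factors predicting the composite. The Sample size calculation section says that precise prior data on the composite do not exist. A scenario with a threefold contrast between women with neither factor and women with one is hard to justify, because every woman enters with at least one risk criterion and many may reach the cervical scan clinic by another route.
- **Chance decides the primary model.** The article calls the adjusted analysis additional, which most naturally means supplementary. It also does not say that the relative risks must be unadjusted, and it assigns chi-squared and t tests to secondary outcomes only.
- **A baseline difference would be found in 40 to 64% of trials.** That figure (1 − 0.95^10 to 1 − 0.95^20) presumes independent 5% tests of 10 to 20 variables. The article states neither a test, a threshold nor a count.

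**Conclusion.** The concern holds in a conditional form and is of moderate severity. The rule is badly fixed: it ties adjustment to observed imbalance in a trial that removes imbalance on two named factors, and it lets the baseline table choose the covariates of any adjusted analysis.

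The cost depends on prognostic strength and prevalence, which the documents do not give. Over assumed odds ratios of 1 to 5 per factor, type I error falls from about 5% to 3%, the log relative risk SE is 0 to 11% too large, and 0 to 6 points of power are given up. At an odds ratio of 1 there is no loss, and adjusting costs nothing either (80.4% against 80.5%). The case for changing the rule therefore does not depend on settling how prognostic the factors are. It matters somewhat more than usual because recruitment was capped by midwife capacity and by the number of eligible women, so precision could not easily be bought with a larger sample.

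**What to change.** Replace the conditional sentence with a fixed rule, for example:

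*The primary analysis estimates the relative risk and risk difference for the composite, adjusted for smoking at booking and previous PTB (< 37 weeks) whatever the observed balance, by modified Poisson regression with robust standard errors or by standardised logistic regression. The unadjusted result is supportive. Covariates are not chosen from observed baseline differences.*

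Delete the trigger. Either name in advance the variables meant by the second, if-necessary sentence or drop that sentence. Use the same two covariates for secondary outcomes where event numbers allow; for rare maternal or neonatal outcomes an adjusted model may be unstable, and an unadjusted estimate is then acceptable.

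The cost is wording in the protocol or analysis plan. Minimisation requires both factors for every woman before allocation, so no new data and no change to the sample size are needed. As recruitment has closed, the change should be dated and made before anyone sees outcomes by arm.

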### Data collection

Demography, medical history and current pregnancy health information and psycho-social health data will be collected prior to randomisation at baseline visit (recruitment). Follow-up data will continue up to 6–8 weeks postpartum for mothers and until discharge from neonatal intensive care unit (NICU) for babies (up to 3 months). Pregnancy outcome, birth and neonatal data will be collected from maternal and infant medical records and NHS electronic data systems. Data from validated questionnaires at baseline and postnatally (e.g. Prenatal Distress Questionnaire [26], Everyday Discrimination Scale [27], PHQ1 Mental Health [28], PROMIS-10 Health Related Quality of Life [28], Labour Agentry Scale [29], Mother-to-Infant Bonding Scale [28, 30], Trust in Nurses Scale [31], Social Support [32]) will be used to assess health and wellbeing, and measure women’s experiences, continuity, quality of care and safety. Data will be anonymised and entered onto the secure, password-protected MedSciNet™.

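### For continuous questionnaire scores measured before randomisation and postnatally, the default is an unadjusted t test, with baseline adjustment only if imbalance or need is perceived

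*Protocol article*

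**What the plan says.** The Data collection section of the protocol article states that "psycho-social health data will be collected prior to randomisation at baseline visit (recruitment"), and introduces its list of instruments with "Data from validated questionnaires at baseline and postnatally". The list is given as examples and is not divided by time point.

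The Proposed statistical analysis section sets the default for secondary outcomes: "continuous data will be analysed with *t* tests (for normally distributed data"). The next sentence treats another data type differently: "Ranked or Likert-scale data will be analysed using cumulative odds ratios".

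Two clauses in that section allow adjustment, both conditionally. The first says that "additional multivariate analysis will be used if baseline differences are noted between the two groups". The second says that "Logistic regression and multiple linear regressions will be used if necessary to adjust for any other confounding variables". Neither names the baseline score of the outcome or the minimisation factors.

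The section on randomisation states that allocation is 1:1 by minimisation on smoking at booking and previous preterm birth.

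**The concern.** A two-sample t test on the postnatal score makes no use of the same woman's score before randomisation. Where the two are correlated, part of the postnatal variation was predictable at entry, and the t test leaves it in the error term. The interval is then wider than the collected data require. The minimisation factors are left out in the same way. If they predict the outcome, balancing on them and then ignoring them makes the standard error larger than it needs to be.

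The conditional clauses do not cure this. They respond to perceived imbalance or confounding, whereas the precision gain exists even when the arms are perfectly balanced. They set no threshold and list no covariates, so each scale has two candidate estimates, and the choice between them is made after the baseline data have been seen.

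The trial asks whether the model of care improves women's experience as well as pregnancy outcomes, and its results are meant to inform a full-scale trial. Psycho-social health is a listed secondary outcome. Estimates as precise as the data allow are therefore useful.

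**Working it through.** **Inputs from the article.** "With 175 women in each arm (350 in total"), 80% power, 40% against 55% for the primary outcome, 1:1 allocation.

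**Assumptions.** Two-sided alpha of 0.05 (not stated). A range for r, the correlation between baseline and postnatal score. The article gives no r, standard deviation (SD) or target difference for any scale, so differences are in SD units.

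**Step 1: the plan's own figure.** With mean proportion 0.475 and difference 0.15:

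n = [1.96 × √(2 × 0.475 × 0.525) + 0.8416 × √(0.40 × 0.60 + 0.55 × 0.45)]² / 0.15² = (1.384 + 0.588)² / 0.0225 = 172.8, so 173 per arm.

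Power at 175 per arm is 80.5%. The stated 80% reproduces. It concerns the binary primary outcome only, so this point leaves it as it is.

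**Step 2: the t test on a continuous scale.** The difference detectable with 80% power at 175 per arm is (1.96 + 0.8416) × √(2/175) = 0.300 SD.

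**Step 3: adjusting for the baseline score.** In large samples the residual variance is multiplied by 1 − r². The detectable difference and the interval width are then multiplied by √(1 − r²), and the t-test sample of equal precision is 175 / (1 − r²) per arm.

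| r | Variance saved | CI width relative to t test | Detectable difference (SD) | Power for 0.30 SD | Equivalent t-test n per arm |
|---|---|---|---|---|---|
| 0 (t test) | 0% | 1.00 | 0.300 | 80.1% | 175 |
| 0.2 | 4% | 0.98 | 0.293 | 81.7% | 182 |
| 0.3 | 9% | 0.95 | 0.286 | 83.7% | 192 |
| 0.5 | 25% | 0.87 | 0.259 | 90.0% | 233 |
| 0.6 | 36% | 0.80 | 0.240 | 93.9% | 273 |

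**Step 4: with incomplete postnatal questionnaires.** Assuming 20% non-response (175 × 0.8 = 140 per arm), the detectable difference is 0.335 SD by t test, and 0.328, 0.319, 0.290 and 0.268 SD after adjustment at r = 0.2, 0.3, 0.5 and 0.6. The relative gain is unchanged.

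**Step 5: which scales this reaches.** The list includes "Labour Agentry Scale [29], Mother-to-Infant Bonding Scale [28, 30"]. Neither labour agentry nor mother-to-infant bonding can have a score from before the birth. By its name, the prenatal distress scale may have no postnatal counterpart. The table therefore applies only to scales given at both times and analysed as continuous; the article does not say which these are. The further gain from the minimisation factors is not quantified, because the article gives nothing on how strongly they relate to any scale.

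**The case against.** The case on the other side has five parts.

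- **Scope of the t test.** A reader might infer that all questionnaire scores go to plain t tests. The article does not say so. The t test is for normally distributed continuous data, and ranked or Likert-scale data go to cumulative odds ratios. This stands, and limits the point to scores treated as continuous.
- **Regression is in the plan.** A reader might infer that the baseline score is shut out of every analysis. It is not: noticed baseline differences trigger adjustment, and linear regression is provided for. What remains is that adjustment is conditional. The section also says the analysis will be blinded. That limits the room for a choice that favours one arm, but it neither fixes the choice in advance nor recovers precision when the arms look balanced.
- **Validity.** A reader might infer biased results. Under randomisation the unadjusted comparison is unbiased, and adjustment is an efficiency gain. This stands in full.
- **Level of detail.** Covariate lists are commonly left to a statistical analysis plan, and this is a condensed article. That would answer a complaint about silence. Here, however, the article names an unadjusted default and makes adjustment conditional, so the point concerns a stated choice.
- **Size.** Women are recruited before 24 weeks' gestation and followed to 6–8 weeks postpartum, with the birth in between. A low r cannot be excluded, and at r = 0.2 the interval narrows by only about 2%. This stands, and is why the range starts there.

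**Conclusion.** The point holds in a limited form. For secondary scales that are treated as continuous and measured at both times, the stated default forgoes precision that costs nothing to obtain, and leaves adjustment to a judgement made on observed data. The loss is 4% to 36% of the variance for r between 0.2 and 0.6. That range is an assumption, and the calculation is the large-sample one. It is a worthwhile improvement to secondary estimates, not a fault that invalidates any result. The article does not support extending it to scales measured only after birth, where there is no baseline score to use.

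**What to change.** State in the analysis section, or in the statistical analysis plan before the data are unblinded:

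- For each continuous scale measured before randomisation and postnatally, the default is linear regression of the postnatal score on allocated arm, baseline score, smoking at booking and previous preterm birth, regardless of observed imbalance. Report the adjusted mean difference with its 95% confidence interval.
- For continuous scales measured only postnatally, adjust for the two minimisation factors.
- For ranked or Likert-scale data, keep the cumulative odds model and add the minimisation factors and, where one exists, the baseline response as covariates.
- List which scales are given at which time point, and which are treated as continuous.
- The unadjusted t test may stay as a sensitivity analysis.

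The cost is a change of wording. Under the plan the baseline scores and both minimisation factors are already collected before allocation, so no new data, visits or participants are needed.
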